# Control of Line Complications with KiteLock (CLiCK) in the critical care unit: study protocol for a multi-center, cluster-randomized, double-blinded, crossover trial investigating the effect of a novel locking fluid on central line complications in the critical care population

**DOI:** 10.1186/s13063-022-06671-5

**Published:** 2022-08-30

**Keywords:** Central venous access device, Catheter locking, Intensive care unit, Central line-associated bloodstream infection, Catheter colonization, Central line occlusion, Catheter-related venous thrombosis, Alteplase, Biofilm, Clinical trial

## Abstract

**Background:**

Insertion of a central venous access device (CVAD) allows clinicians to easily access the circulation of a patient to administer life-saving interventions. Due to their invasive nature, CVADs are prone to complications such as bacterial biofilm production and colonization, catheter-related bloodstream infection, occlusion, and catheter-related venous thrombosis. A CVAD is among the most common interventions for patients in the intensive care unit (ICU), exposing this vulnerable population to the risk of nosocomial infection and catheter occlusion. The current standard of care involves the use of normal saline as a catheter locking solution for central venous catheters (CVCs) and peripherally inserted central catheter (PICC) lines, and a citrate lock for hemodialysis catheters. Saline offers little prophylactic measures against catheter complications. Four percent of tetrasodium ethylenediaminetetraacetic acid (EDTA) fluid (marketed as KiteLock Sterile Locking Solution™) is non-antibiotic, possesses antimicrobial, anti-biofilm, and anti-coagulant properties, and is approved by Health Canada as a catheter locking solution. As such, it may be a superior CVAD locking solution than the present standard of care lock in the ICU patient population.

**Methods:**

Our team proposes to fill this knowledge gap by performing a multi-center, cluster-randomized, crossover trial evaluating the impact of 4% tetrasodium EDTA on a primary composite outcome of the incidence rate of central line-associated bloodstream infection (CLABSI), catheter occlusion leading to removal, and use of alteplase to resolve catheter occlusion compared to the standard of care. The study will be performed at five critical care units.

**Discussion:**

If successful, the results of this study can serve as evidence for a shift of standard of care practices to include EDTA locking fluid in routine CVAD locking procedures. Completion of this study has the potential to improve CVAD standard of care to become safer for patients, as well as provides an opportunity to decrease strain on healthcare budgets related to treating preventable CVAD complications. Success and subsequent implementation of this intervention in the ICU may also be extrapolated to other patient populations with heavy CVAD use including hemodialysis, oncology, parenteral nutrition, and pediatric patient populations. On a global scale, eradicating biofilm produced by antibiotic-resistant bacteria may serve to lessen the threat of “superbugs” and contribute to international initiatives supporting the termination of antibiotic overuse.

**Trial registration:**

ClinicalTrials.gov NCT04548713, registered on September 9th, 2020.

**Supplementary Information:**

The online version contains supplementary material available at 10.1186/s13063-022-06671-5.

## Administrative information

Note: The numbers in curly brackets in this protocol refer to SPIRIT checklist item numbers. The order of the items has been modified to group similar items (see http://www.equator-network.org/reporting-guidelines/spirit-2013-statement-defining-standard-protocol-items-for-clinical-trials/).

## Introduction

### Background and rationale {6a}

Insertion of a central venous access device (CVAD) is an essential medical intervention, allowing clinicians to access the circulation of a patient and administer life-saving interventions. Due to their invasive nature, CVADs are prone to complications such as occlusion, and bacterial colonization of the CVAD that may travel to the bloodstream and cause infection, known as central line-associated bloodstream infection (CLABSI). A CVAD is among the most common interventions in the intensive care unit (ICU) [1] exposing this vulnerable population to potential hospital-acquired infections and CVAD occlusion.

A recent systematic review identified pooled estimates for CLABSI at 4.59 per 1000 catheter days based on calculations from global databases and studies in adult ICUs [2]. This is well above the global target of zero [3]. Significant risk factors associated with developing CVAD-related infection include longer duration of CVAD insertion, administration of total parenteral nutrition, presence of multiple CVADs, and use of CVADs that have multiple lumens [4]. Unfortunately, all of these risk factors are common among ICU patients and often cannot be modified due to clinical needs. It is also known that bacteria that colonize the CVAD aggregate into microcolonies known as biofilm, which exhibit different properties than single units of bacteria and result in a much more difficult to treat infection [5].

In addition to posing a significant risk to the patient, hospital-acquired bloodstream infections are associated with an increased median length of stay of 2 days and a $12,321 increase per case costs in Canadian ICUs, when compared to matched-cohort controls [6]. The most recent report by the Canadian Nosocomial Infection Surveillance Program states a combined incidence rate of 159 CVAD-associated bloodstream infections diagnosed annually in the 54 participating hospitals, costing the healthcare system an estimate of $2,000,000 each year [7]. As not all Canadian hospitals contribute to this reporting, and CLABSI diagnosis criteria may vary between hospitals, this is likely an underestimation of the total cost to the Canadian healthcare system.

In addition to bacterial colonization and infection, CVADs are prone to the formation of thrombi (blood clots) that may occlude the CVAD [5, 8, 9]. A CVAD may also become occluded due to an accumulation of precipitate from medication or parenteral nutrition, or a build-up of biofilm [10, 11]. CVAD occlusion is common, affecting approximately between 14 and 36% of all CVADs [12]. In addition to interrupting treatment through the CVAD, a thrombus may dislodge into the bloodstream and cause further adverse events such as a thromboembolism, or spread an attached bacterial biofilm into the bloodstream [5, 8, 9]. Current treatment of catheter occlusions involves the use of costly thrombolytic agents such as alteplase—the cost of which has more than doubled between 2005 and 2014 and is now priced at $63.40 per dose  [13]. Although expensive, Ernst and colleagues determined treatment with alteplase to cost an average of $317 less per patient compared to complete catheter replacement [12]. As such, effective prevention of CVAD occlusion provides an opportunity to significantly decrease the cost and morbidity associated with ICU care.

Appropriate CVAD care is paramount in preventing infection and occlusion. The current standard of care in the intensive care unit (ICU) involves the use of salt water (saline) as a locking solution for central venous catheters (CVCs) and peripherally inserted central catheters (PICC lines). Although adequate in maintaining patency, saline offers no anti-bacterial or anticoagulant properties that may act as prophylactic measures against infection and occlusion. Hemodialysis lines are locked with citrate. Evidence from the literature shows alternative locking solutions with additional protective properties such as the use of antibiotic, heparin, citrate, or ethanol locks are not efficacious and are costly in terms of unnecessary patient risk, the propagation of antibiotic overuse, and excess cost to the healthcare system [14–22].

Successful prevention of catheter complications requires simultaneous inhibition of bacterial colonization, biofilm formation, and thrombus formation. Four percent of tetrasodium ethylenediaminetetraacetic acid (EDTA) is a fluid that possesses non-antibiotic, anti-microbial, anti-biofilm, and anti-thrombotic properties [23, 24]. As such, it may serve to fill this need when investigated as a locking fluid. Four percent of EDTA (known as “KiteLock 4% Sterile Catheter Lock Solution”) is already approved by Health Canada as a catheter lock solution. In the laboratory environment, microbial biofilm isolates from 12 common CVAD colonizing bacterial and fungal species were completely eradicated by 4% EDTA [25]. Clinical investigations have shown 4% EDTA to reduce CVAD complications in pediatric intestinal failure patients and hemodialysis patients [26–28]. The results of these studies demonstrate a decrease in CLABSI rates from 2.7 to 0 cases per 1000 catheter days and from 1.9 to 0.6 per 1000 catheter days after 12 months of use [27, 28]. Four percent of EDTA has not yet been studied in the particularly vulnerable intensive care population. We propose to conduct a multi-center study to assess the efficacy of 4% EDTA in preventing CVAD infection and occlusion when used as a locking fluid. If successful, this intervention may serve to reduce the risk associated with ICU stay, thus contributing to reduced morbidity and mortality. Furthermore, this intervention may serve to reduce the cost associated with CVAD complication treatment and contribute to worldwide efforts to lessen reliance on antibiotics.

## Objectives {7}

### Primary objectives

The primary objective is to compare the incidence rate of CLABSI, catheter occlusions requiring replacement, and alteplase use present in critical care patients with CVADs locked with 4% tetrasodium EDTA versus critical care patients with CVADs locked with the standard of care of saline or citrate.

For the purpose of this study, these outcomes will be evaluated using a composite outcome consisting of the incidence rate of catheter obstruction requiring alteplase, CLABSI (diagnosed in accordance with NHSN definitions [29]), or CVAD replacement due to occlusion. As current surveillance guidelines do not include routine CVAD occlusion reporting, the use of alteplase specifically for the treatment of CVAD occlusion has been identified as a proxy method to track the occlusion rates.

The secondary objectives include the incidence rate of each component of the composite outcome separately, and other outcomes that may be modifiable with change to catheter locking practices, including: the incidence of catheter colonization (as identified by the standard clinical and microbiology operating procedures at each institution enrolled in the study), incidence of catheter-associated venous thrombosis, direct cost related to alteplase use for catheter occlusion, other costs related to treatment and diagnosis of relevant CVAD complications, and classification of microbial species isolated from colonized catheters.

### Trial design {8}

The trial is a multi-center, cluster-randomized, double-blinded, crossover trial. Five ICUs/high acuity units (HAUs) across Canada will participate. The ICU/HAUs will be assigned at random to administer either the 4% EDTA locking solution (intervention) or the standard of care saline or citrate (control) during the first four-and-a-half-month period. ICU/HAUs will then cross over and administer the other locking solution during the second 4.5-month period. Patient recruitment will cease at the end of three-and-a-half months during each period to ensure all patients can be followed for 28 days. The study protocol will commence at each site via a staggered start (see Fig. 1).

**Fig. 1 Fig1:**
[figure not shown]
Study protocol

## Methods: participants, interventions, and outcomes

### Study setting {9}

This study will take place in five ICU/HAUs in hospitals located across Canada. Participating sites include Royal Columbian Hospital, Surrey Memorial Hospital, Royal Jubilee Hospital, Nanaimo Regional General Hospital, and St. Boniface Hospital.

### Eligibility criteria {10}

The following are the inclusion criteria:ICU/HAU admission.Presence of a central venous catheter requiring locking. This includes triple lumen central venous catheters (both tunneled and non-tunneled), dialysis lines, implanted vascular access devices (IVADs), and peripherally inserted central lines (PICCs).18 years of age.

The following are the exclusion criteria:Known sensitivity to EDTA.Confirmed or suspected pregnancy, as 4% tetrasodium EDTA has not yet been investigated for use in the pregnant population.Patients who decline receiving blood products (due to the smaller blood draws and special blood conserving procedures).Physician, patient, or temporary substitute decision-maker (TSDM) declines.Currently enrolled in any other research study that may confound primary outcome measures. Co-enrollment in multiple studies will be considered on an individual basis.Patients who were previously enrolled in the study. Patients who were enrolled in the first period are not eligible for (re-)enrollment in the second period, and patients who are enrolled in the study and transferred to another participating hospital are not eligible for (re-)enrollment at the receiving hospital. Patients who had been discharged from the unit to another hospital ward and are re-admitted to the critical care unit are not eligible for re-enrollment into the study.

### Who will take informed consent? {26a}

Under the guidance of the Tri-Council Policy Statement 2, this study has been approved for a waiver of consent (under Article 3.7A) by relevant ethics boards for the following reasons: 4% tetrasodium EDTA is considered at least as safe as the standard of care and has Health Canada approval, there is a strong chance that 4% tetrasodium EDTA will be safer than the standard of care, there have been no adverse outcomes reported in previous clinical use, and the study could not be feasibly completed with a deferred or a full consenting process due to the rapid decision to use a CVAD lock and the need to use it immediately. Due to practical barriers caused by the volume of patients enrolled in the study, it will not be possible for the research staff to inform all patients of their participation in the clinical trial once treatment is finished.

Reminders and signage relevant to the trial will be present in each unit during study procedures. Should patients or caregivers have questions about the trial, a patient/caretaker information letter will be provided along with contact information for the research coordinator. Patients/caretakers will be informed that they can remove themselves or their family members from the trial at any time, with no consequence to their care.

### Additional consent provisions for collection and use of participant data and biological specimens {26b}

This trial does not involve collecting biological specimens for storage (see item {33}).

### Interventions

#### Explanation for the choice of comparators {6b}

The comparator to the trial intervention will be the standard of care CVAD lock. This includes saline for central venous catheters and peripherally inserted central catheters, and citrate for hemodialysis catheters. As the aim of the study is to determine whether 4% EDTA is more efficacious in preventing CVAD complications than the current standard of care, we must compare this alternative to current practices.

#### Intervention description {11a}

Upon admission to the ICU/HAU, any patient with a CVAD requiring locking who meets the criteria will be enrolled in the study. The patient will receive either a standard of care lock or a 4% tetrasodium EDTA locking solution depending on the randomization status of their treating hospital. Syringes containing either 4% tetrasodium EDTA solution or standard of care locking fluid to be used during locking procedures (called “locking kits”) will be prepared ahead of time by the research pharmacy according to the randomization status of the unit. They will be clearly labeled for use as a locking solution only and placed at the patient’s bedside. Syringes will be prepared with an additional label to remind nurses not to use them in pregnant patients or in those who decline any blood products. In addition to the bedside assessment, research coordinators will review each patient that has received a locking solution every day to gather data and to ensure compliance with the study protocols. Nurses will use the prepared syringes to lock and maintain each CVAD according to the standard of care. Syringe supply at each patient’s bedside will be replenished as needed by the research pharmacy and research coordinators. Enrollment can occur 24 h per day, 7 days per week as nurses can obtain locking syringes specific to the randomization status of the unit at all times.

Medication, maintenance fluids, pressors, or anesthesia will be administered through the CVAD according to the standard of care. Once a lumen of the catheter is no longer being utilized for continuous infusions, leftover medication will be aspirated and flushed with 20 mL of 0.9% sodium chloride using a turbulent flush method as per the standard of care. For patients randomized into the experimental group, the catheter will then be locked with the appropriate volume of 4% tetrasodium EDTA, as specified by catheter manufacturer instructions. These procedures will remain exactly the same for patients randomized into the control group with the exception of using saline or citrate as a locking fluid. Experimental and control solutions are indistinguishable by visual inspection.

All further catheter procedures and maintenance will proceed according to the standard of care. For all locked catheters, the frequency of flushing will occur every 12 h (or 72 h for dialysis catheters). During this procedure, catheters locked with the standard of care lock will be aspirated, flushed with 10 mL of 0.9% sodium chloride using turbulent flow, and re-filled with the appropriate volume of the standard of care lock. Procedures will stay exactly the same for patients in hospitals randomized to administer the 4% tetrasodium EDTA treatment, except for continued locking with 4% tetrasodium EDTA. Neutral displacement cap change procedures will remain unchanged in both groups. This includes a change every 96 h, after a blood draw through a cap, if removed, contaminated, damaged, and as needed.

Regular assessments of the site of insertion, CVAD system, and patency will continue according to the standard of care, regardless of the type of locking solution used. According to the adult CVAD maintenance record used at each hospital, nurses will assess that dressing is secure, dry, and intact and will palpate the site and check the system at the beginning of each shift. The site of insertion and connections will be reassessed every 4 h as is standard protocol. Dressing and tubing changes will also proceed according to the standard of care in both groups.

Should a locked line (locked with either standard of care or 4% tetrasodium EDTA solution) needs to be re-opened for additional medication administration, the line will be assessed for patency, aspirated of locking solution, and flushed with 20 mL of 0.9% sodium chloride before administering further medication. Patency will be assessed by the ability to aspirate for blood return and the ability to flush a CVAD without resistance prior to the administration of medications and solutions. If the line is not patent, the nurse will assess for occlusions and proceed with the standard of care occlusion diagnosis and treatment. As per the standard of care, CVADs will continue to be removed at the earliest opportunity for each patient. Four percent of EDTA has been shown to be safe if it is inadvertently flushed into the patient, thereby ensuring an adequate safety profile for use with these vulnerable patients.

#### Criteria for discontinuing or modifying allocated interventions {11b}

The patient may withdraw from the trial at any time. Patients for whom an exclusion criterion is discovered after enrollment will be withdrawn from the study and excluded from the analysis.

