#### Strategies to improve adherence to interventions {11c}

The patients themselves do not have to do anything to adhere to the intervention or provide measurements of primary and secondary outcomes. The intervention itself will be administered by the ICU/HAU staff at each center. Strategies to ensure the staff adhere to the experimental procedures include education sessions on the purposes and procedures of the trial before the start of the experiment, and during the trial. The ICU/HAU staff have also been a part of the protocol development to ensure a seamless incorporation of experimental procedures into the standard workflow. The primary and secondary outcomes are already captured as part of the standard of care and will be recorded in patient charts. These charts will be reviewed by the research staff to fill out the study case report forms (CRFs).

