### Assignment of interventions: blinding

#### Who will be blinded {17a}

Trial participants, care providers, outcome assessors, and data analysts will be blinded to the assignment of intervention. The only research personnel who will be unblinded are the statistician performing the randomization, the PM, and the research pharmacists in charge of supplying locking kits used during the study. As each of the 4% tetrasodium EDTA, saline, and citrate will be placed in 10mL syringes, they will not be distinguishable to the trial participants, care providers, or outcome assessors to maintain their blinding. Data analysis will occur outside of the unit with the type of intervention received by each patient concealed until the completion of analysis.

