## Statistical methods

### Statistical methods for primary and secondary outcomes {20a}

Data will be analyzed following the intent-to-treat principle. The primary outcome will be analyzed using a zero-inflated negative binomial (ZINB) model that accounts for clustering within ICU [33]. The ZINB model takes into account: (1) the large percentage (~ 80% expected) who will not have any event and (2) the large variability in the number of events among participants who experience at least one event (individuals who experience one event are more likely to experience additional events). The (log-)time-at-risk will be entered into the model as an offset term. The average treatment effect will be obtained by regression standardization of the composite incidence rates predicted by the ZINB model [34]. Standard errors will be obtained using bootstrapping.

The model will adjust for the study period (first or second) and may adjust for the following individual-level baseline characteristics: age; sex at birth; BMI; APACHE IV score; length of pre-ICU hospital stay (days); presence of multiple CVADs per patient; any suppression of the immune system, defined as post-organ transplantation, acquired immunodeficiency syndrome [AIDS], neutropenia [< 1000 absolute neutrophils], corticosteroids [> 20 mg/day of prednisone or equivalent for more than 6 months], or currently taking immunosuppressive agents (i.e., Imuran, etc.) at time of enrollment into study; site of CVAD insertion (femoral, jugular, subclavian, right or left side); type of catheter used; any catheter additives, as they may confound the result (such as antibiotic impregnation); having a pre-existing central line upon admission to the ICU; and this line had already received a lock, concurrent systemic antibiotic use unrelated to central line infection, concurrent systemic anti-fungal agent use unrelated to central line infection, concurrent systemic administration of anti-coagulants unrelated to catheter occlusion, type of hemodialysis (if applicable), and previously experienced CLABSI or CVAD occlusion.

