#### Adverse event reporting and harms {22}

Information about any AEs will be collected with routine data collection. AEs will include (1) local site irritation or redness following accidental administration of the catheter lock into the patient circulation, (2) dysgeusia following accidental administration of the catheter lock into the patient circulation, (3) paresthesia following accidental administration of the catheter lock into the patient circulation, (4) pain upon accidental administration of the catheter lock into the patient circulation, (5) “head rush” following administration, (6) blood rush to face and lips following administration, (7) hypocalcemia due accidental administration of the catheter lock into the patient circulation, and (8) any other adverse reaction observed during accidental administration of the catheter lock into the patient circulation.

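### Dropping enrolled patients from the analysis when an exclusion criterion surfaces later conflicts with intention-to-treat, and the rule has no time limit or blinded decision

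*Protocol article*

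**What the plan says.** Item 11b of the protocol article, on discontinuing or modifying allocated interventions, has two sentences. The first lets a patient withdraw whenever they wish and attaches no consequence for the analysis. The second reads: "Patients for whom an exclusion criterion is discovered after enrollment will be withdrawn from the study and excluded from the analysis".

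Item 20a, on statistical methods, says: "Data will be analyzed following the intent-to-treat principle". It describes no modified population and does not refer back to item 11b.

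Two of the exclusion criteria in item 10 matter most here: "Known sensitivity to EDTA" and "Physician, patient, or temporary substitute decision-maker (TSDM) declines". Consent is waived, and under item 26a "Patients/caretakers will be informed that they can remove themselves or their family members from the trial at any time". Item 22 collects reactions to the lock as adverse events, ending with "any other adverse reaction observed during accidental administration of the catheter lock into the patient circulation". On masking, item 17a states: "Trial participants, care providers, outcome assessors, and data analysts will be blinded to the assignment of intervention".

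**The concern.** Intention-to-treat keeps each enrolled patient in the group to which the ICU was assigned in that period. Item 11b removes some of them, with all their events and catheter days. Both statements cannot define the primary analysis set.

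Excluding patients who were ineligible before treatment, on a blinded judgement, is a commonly accepted modified intention-to-treat approach. Item 11b does not confine itself to that. It turns on when the criterion is discovered, not on when it arose, and says nothing about who decides or what they know. Late discovery is to be expected: enrolment runs round the clock under waived consent, a pregnancy result is needed only if a test was done, and co-enrolment is judged case by case.

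As worded, the rule leaves two readings open:

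- A sensitivity first revealed by the study lock could count as a discovered criterion. After enrolment the study lock can reveal this only in EDTA periods.
- A refusal by physician, patient or family after the first lock could count as the criterion about declining.

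Either would make membership of the analysis set depend on events after treatment started. At stake are a clearly defined primary population and, if removals were numerous and one-sided, the treatment estimate itself.

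**Working it through.** **Reproducing the plan's sample size.** Inputs from item 14: 20% against 14%, 1690 patients, cluster-period SD 0.001, and degrees of freedom equal to cluster periods minus periods minus one. Five ICUs and two periods give 10 − 2 − 1 = 7 df and 1690/10 = 169 patients per cell. The stated simulation error of 0.4% implies 80% power, since √(0.8 × 0.2/10,000) = 0.0040. Two-sided alpha of 0.05 is assumed, as it is not stated.

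- Variance of the mean within-ICU difference: (0.20 × 0.80/169 + 0.14 × 0.86/169 + 2 × 0.001²)/5 = 0.000332, so SE = 0.0182.
- Noncentrality: 0.06/0.0182 = 3.29. The noncentral t with 7 df gives power of 80.5%. Simulation gave 81.1%.
- Stated correlation: the mean of 0.02²/0.16 = 0.0025 and 0.02²/0.1204 = 0.0033 is 0.0029, as in the plan.

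The 1690 reproduces, and the fix does not alter it.

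**Power cost of exclusions balanced between arms.** Same formula with fewer patients per cell:

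| Dropped | Power from 1690 |
|---|---|
| 0% | 80.5% |
| 1% | 80.1% |
| 2% | 79.7% |
| 5% | 78.5% |
| 10% | 76.4% |

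This is about 0.4 points per 1% dropped. Expected enrolment of 1750 leaves 1750 − 1690 = 60 patients in hand. Power is not the issue.

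**Bias if removals fall only in EDTA periods.** The article gives no figures, so x (fraction removed) and q (event risk of those removed) are assumed. With true EDTA-arm risk p, the observed risk is (p − xq)/(1 − x). Take no true effect, p = 0.20 in both arms, and 1690/2 = 845 patients per arm:

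| x | Patients | q | Observed EDTA risk | Risk ratio | Type I error |
|---|---|---|---|---|---|
| any | – | 20% | 20.0% | 1.00 | 5.0% |
| 1% | 8 | 40% | (0.20 − 0.004)/0.99 = 19.8% | 0.99 | 5.1% |
| 2% | 17 | 40% | (0.20 − 0.008)/0.98 = 19.6% | 0.98 | 5.4% |
| 2% | 17 | 60% | (0.20 − 0.012)/0.98 = 19.2% | 0.96 | 6.5% |
| 5% | 42 | 40% | (0.20 − 0.020)/0.95 = 18.9% | 0.95 | 7.5% |
| 5% | 42 | 60% | (0.20 − 0.030)/0.95 = 17.9% | 0.89 | 15.3% |

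The error rates come from the noncentral t with 7 df and a 3:2 split of ICUs between sequences. They assume a test that holds 5% without exclusions. A simulated logistic model judged against the 7-df critical value rejected in only 2.1% of null trials, so these rates are approximate.

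If the planned effect is real (p = 0.14), removing 2% at 42% risk gives (0.14 − 0.0084)/0.98 = 13.4%, a ratio of 0.67 instead of 0.70. Removing 5% at 42% gives (0.14 − 0.021)/0.95 = 12.5%, a ratio of 0.63.

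**Events per catheter day.** The primary outcome is a rate. If removed patients hold a fraction f of the EDTA-arm catheter days and have k times the arm's rate, the observed rate is multiplied by (1 − fk)/(1 − f). With f = 5% and k = 3 this is 0.85/0.95 = 0.89, matching the last row. The share of catheter days is what counts, and k below 1 would bias against EDTA.

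**The case against.** A reader might infer that item 11b will strip EDTA reactors and dissatisfied families out of the EDTA arm and erase the product's adverse reactions. The article does not support that, for four reasons.

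- A known sensitivity most naturally means a fact that already existed and was missed at a hurried enrolment. Table 1 has eligibility confirmed at baseline. Reactions to the lock have their own route as adverse events, and nothing reclassifies them as exclusion criteria.
- Item 11b deals with voluntary withdrawal in a separate sentence that does not remove the patient from the analysis.
- Patients, staff, assessors and analysts are masked, the solutions look alike, and codes are broken only in emergencies. Pregnancy, refusal of blood products and earlier enrolment have nothing to do with the lock, so removals on those grounds should be roughly balanced.
- Adverse events are collected routinely, reviewed by the principal investigator, reported to ethics boards and tabulated. No text discards those of withdrawn patients.

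It can also be said that analysis sets are commonly defined in the statistical analysis plan, which is promised before unblinding.

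Most of this stands, and it makes large arm-selective loss unlikely. It does not remove the conflict. The article states a rule instead of leaving one open, and its wording does not exclude the two readings described under the concern. Masking also has a limit: every patient in an ICU receives the same solution in a period, so one emergency unblinding reveals the allocation of all of them.

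**Conclusion.** The concern holds as a conflict between items 11b and 20a and as a rule worded too loosely. It does not show that the trial will be biased. The article gives no expected number of such patients, and every bias figure here rests on assumed removal rates, assumed risks and removal from one arm only. On those assumptions the effect is nil when removed patients have average risk and negligible at about 1% removed with moderately higher risk. It becomes material only near 5% (about 42 of 845), with those patients at well above average risk. The loss of power is minor, and the 60-patient margin adds little to the argument. This is a clarification worth making before unblinding, not a threat to the design.

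**What to change.** Reconcile items 11b and 20a, in the protocol and in the statistical analysis plan:

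- The primary analysis includes every enrolled patient under the lock assigned to their ICU and period.
- The only permitted exclusion is for a criterion documented as present before the first lock, judged by someone blind to allocation and outcome.
- Patients who later decline or react contribute events and catheter days up to withdrawal, as far as ethics approval allows.
- All adverse events in patients who received a lock stay in the safety tabulation.
- Exclusions are reported by arm and reason.
- The present rule is run as a sensitivity analysis.

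The cost is about a paragraph of text. Little extra data collection is needed, because item 11c notes: "The primary and secondary outcomes are already captured as part of the standard of care and will be recorded in patient charts". The drawback is that a few ineligible patients remain in the analysis. Whether to stop the study lock in such patients is a separate clinical matter and need not decide who is analysed.
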